### Eligibility and recruitment

#### Recruitment

Recruitment is undertaken by the community hepatitis nurses at each study site.

### Study assessments

Following randomization, participants complete assessments during the study as outlined in the schedule of assessments (see Fig. 2).

**Fig. 2 Fig2:**
[figure not shown]
Study schedule

This includes pre-treatment assessment blood tests and TE, and then a clinical review and blood tests at: baseline, on treatment at weeks 2, 4, 8, 12, and post-treatment weeks 12, 24 and 48 weeks, subject to local national guidelines. The visits post treatment at week 24 and 48 are to assess for HCV re-infection. TE is performed pre-treatment and may be incorporated into an appointment, or may be a stand-alone appointment, according to the clinic’s usual practice. Detailed questionnaires are collected at screening and 12 weeks post treatment. Participants are reimbursed AU$20 at the screening visit, and AU$40 at the visit 12 weeks post treatment. Data from assessments is collected on clinical research forms identified only by study number, and entered into REDCap database at Australian sites, or entered directly into REDCap database at New Zealand sites.

### Data sources

At screening and 12 weeks post treatment, the following data is collected:

Demographic characteristics including: age, sex, race and ethnicity, education level, employment status, main income source, average weekly income, living arrangements, type of accommodation and incarceration history.

Drug use including: history of injecting drug use, frequency and substance injected, presence of injecting partners, sharing of injecting drug equipment, receipt of OST, frequency and quantity of alcohol consumed via the AUDIT-C questionnaire.

Health, wellbeing and quality of life indices as measured by the following standardized instruments: the Personal Wellbeing Index, EQ-5D-3 L, 12-item Short Form Health Survey (SF-12) and Patient Health Questionnaire (PHQ-SADS).

At 12 weeks post treatment, customer satisfaction data is collected.

At clinical appointments, the following data is collected: patient-reported adherence to medication, use of a dosette box, administration of medication by a carer or patient, if on OST (and if so frequency of pick-up), AUDIT-C questionnaire regarding alcohol, frequency of injecting drugs and sharing injecting drug equipment, results of pathology tests, any alteration to medication regimen and if the participant has received transport or healthcare worker assistance to attend the appointment.

In addition, data will be collected from the healthcare services participant failure to attend scheduled study appointments.

### Study outcomes

*Primary outcome:*
The proportion of people attending a PHCS with chronic HCV who commence DAA therapy at their PHCS, and achieve SVR12

*Secondary outcomes:*
2.The difference in the proportion of participants commencing DAA therapy between group 1 (standard tertiary care arm), and group 2 (intervention PHCS arm)3.The difference in the proportion of participants achieving SVR12 between group 1 (standard tertiary care arm), and group 2 (intervention PHCS arm)4.To determine the cascade of care for people with HCV referred to a community hepatitis nurse, measured by the proportion who (1) complete TE, (2) complete blood tests, (3) start treatment (defined as a script being written) and (4) achieve SVR12. Time between diagnosis, assessment and treatment will be determined

### Sample size and power considerations

We designed a non-inferiority study to examine SVR12 outcomes of people treated in a PHCS, and to estimate the effect of providing DAA treatment in PHCS on treatment uptake using intention-to-treat analysis. Prior to the introduction of PEG-free therapy, approximately 10% of people with HCV who attended a PHCS commenced HCV treatment. Of those people, 70% completed therapy, which had an SVR12 rate of 85% [20]. We estimated that the number of people who commenced HCV treatment would substantially increase with DAA therapy to approximately 50% for people managed at PHCS, and 30% for people that attend tertiary hospitals. We attributed most of this difference to loss to follow-up after referral from the PHCS to the tertiary hospital, but before tertiary hospital attendance. We anticipated that 90% would be cured, regardless of whether they are treated at a PHCS or tertiary hospital, and that participants would have high levels of adherence [21].

Based on data from other community cohorts, we estimated 20% of participants would have screening TE results greater than 9.5 kPa, and would be excluded after being randomized. Given these response parameters and equal allocation across study groups, we estimated that 190 study participants were required in each arm in order to address the primary aim of the study and provide sufficient power for secondary aims.

*Aim 1: To determine if SVR12 outcomes of people treated in a PHCS are non-inferior to SVR12 achieved by historic controls.*

In keeping with initial DAA trials, our intervention arm was compared to historical controls [22, 23]. We hypothesized that the rate of SVR12 in people receiving DAA treatment in a PHCS would be non-inferior when compared to an SVR12 rate of 85% for historic controls treated with PEG, ribavirin and simeprevir. A sample of 76 (50% of 152) participants commencing DAA treatment at the PHCS would give a minimum of 90% power to show non-inferiority in those receiving DAA therapy using a 10% margin and an expected SVR12 response of 90% (one-sided α of 2.5%).

*Aim 2: To measure the difference in the proportion of people with HCV infection attending a PHCS who commence DAA treatment, if they are managed at their PHCS, compared to those who are referred to and managed at a tertiary hospital.*

Assuming that 30% of participants in group 1 (standard tertiary care arm) start treatment, our expected sample was powered (80%, 5% significance level) to detect an absolute minimum difference of 16% in treatment initiation between the arms.

*Aim 3: To measure the difference in the proportion of people with HCV infection attending a PHCS who achieve SVR12, if they are managed at their PHCS, compared to those who are referred to and managed at a tertiary hospital.*

Assuming that 27% of participants in group 1 (standard tertiary care arm) achieved SVR12, our expected sample was powered (80%, 5% significance level) to detect an absolute minimum difference of 15.3% between arms.

*Aim 4: To use mathematical modeling, informed by outcomes 1–4, to estimate the reduction in HCV prevalence and corresponding epidemiological impact if service delivery through PHCS was scaled up to a country level.*

We hypothesize that the reduced loss to follow-up and increased treatment uptake when services are delivered through PHCS will result in greater prevalence reduction and reduced incidence compared to projections based on standard tertiary care.

*Aim 5: To use mathematical modeling, informed by outcomes 1–4, to estimate the difference in total healthcare costs, difference in disability-adjusted life years (DALYs), and incremental cost-effectiveness ratio (ICER; AU$ per DALY averted) if service delivery was changed nationally from the standard tertiary care to PHCS delivery.*

This will be based on existing models that account for the costs and DALYs accrued as a result of untreated and progressing liver disease over time [24, 25]. We hypothesize that PHCS delivery will be cheaper than standard tertiary care, and result in fewer DALYs.

### Statistical analyses

For the primary aim (aim 1), an exact one-sided binomial hypothesis test will be undertaken to determine non-inferiority of DAA treatment in PHCS in terms of SVR12 response. For study aims 2 and 3, given the individual-level randomized nature of the design, Pearson chi-square tests [26] of independence will be undertaken in comparing differences in DAA therapy initiation and SVR12 across the two study groups. Statistical analyses will be performed using Stata version 13.0 [27].

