**Methods:**

Consenting patients with HCV infection attending 13 PHCS in Australia or New Zealand are randomized to receive DAA treatment at the local tertiary institution (standard care arm), or their PHCS (intervention arm). The primary endpoint is the proportion commenced on DAAs and cured. Treatment providers at the PHCS include: hepatology nurses, primary care practitioners, or, in two sites, a specialist physician. All PHCS offer opioid substitution therapy.

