### Randomization

Although patients are randomized at the end of the screening visit, a unique feature of this study is that randomization occurs before all screening procedures are complete. This is because pre-treatment assessment, which consists of blood tests and transient elastography (TE) (FibroScan**®,** Echosens), is a key part of the care cascade, and given that TE is not readily available in Australia or Auckland, in these study sites the location of TE is determined by the randomization result (see Fig. 1a). In Christchurch, TE is readily available in the community, and participants undergo TE at their PHCS as part of the screening visit (see Fig. 1b).

Participants are randomized to the two study arms using a block randomization approach. Randomization occurs at the PHCS level, to ensure equal numbers of patients from each PHCS are randomized to each arm. Random sequences of permuted blocks are generated, with each block allocating six study participants in a balanced fashion across treatment groups. Randomization is programmed using Stata version 13.0 and provided to study staff in sealed envelopes (Australian sites) or via REDCap database (New Zealand sites).

After the pre-treatment assessment has been completed, the results are reviewed in a follow-up appointment located at the tertiary hospital for group 1, and the PHCS for group 2. Eligible patients are then able to commence DAA treatment.

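### Allocation is blocked within each PHCS, but Aims 2 and 3 use an unstratified chi-square: conservative and slightly inefficient if uptake differs between sites, though still valid and adequately powered

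*Protocol article*

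**What the plan says.** All passages are in the Protocol article.

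- Abstract, Methods: "Consenting patients with HCV infection attending 13 PHCS in Australia or New Zealand are randomized" to tertiary care or to their PHCS.
- Randomization: "Randomization occurs at the PHCS level, to ensure equal numbers of patients from each PHCS are randomized to each arm". Permuted blocks are used, "with each block allocating six study participants in a balanced fashion across treatment groups". PHCS is therefore the stratum within which individuals are allocated.
- Statistical analyses, for Aims 2 and 3: "given the individual-level randomized nature of the design, Pearson chi-square tests [26] of independence will be undertaken in comparing differences" between the two groups. No stratified test, site term or site-adjusted estimate is named.
- Sample size and power considerations: "we estimated that 190 study participants were required in each arm", and "we estimated 20% of participants would have screening TE results greater than 9.5 kPa, and would be excluded after being randomized". Aim 2 is powered at 80%, 5% significance level, for a 16-point difference from 30%. Aim 3 is powered likewise for 15.3 points from 27%. The expected uptake is 50% against 30%.

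**The concern.** The reason given for the chi-square test is that individuals, not sites, are randomized. That explains why no correction for cluster allocation is needed. It does not explain why the stratum used for allocation is left out of the analysis.

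The article describes reasons why uptake may differ by site. Transient elastography is done before randomization in Christchurch and at an arm-dependent location elsewhere. Provider type varies, and New Zealand recruits genotype 1 only. Blocking keeps such differences out of the arm comparison, but the pooled chi-square variance still counts them as noise.

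Aims 2 and 3 are the trial's only randomized between-arm comparisons, so precision lost there is worth recovering if it costs little. The test and its rationale are stated in the article, so this is a comment on a stated choice and not on a detail left to a fuller plan.

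**Working it through.** **Inputs.** From the article: 13 sites; blocks of six, 1:1; 190 per arm; 20% excluded after randomization; control rates of 30% (Aim 2) and 27% (Aim 3); detectable differences of 16 and 15.3 points; expected difference 50% − 30% = 20 points. Assumed: a two-sided 5% level, the between-site SD of uptake, and within-site balance that survives the exclusions.

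**Step 1: the plan's own figures.** Evaluable per arm: 190 × 0.80 = 152, which agrees with "A sample of 76 (50% of 152) participants commencing DAA treatment at the PHCS".

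Power = Φ[(d − 1.96·SE0)/SE1], where SE0 = √(2p̄(1−p̄)/n) and SE1 = √([p1(1−p1) + p2(1−p2)]/n).

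- Aim 2, 30% vs 46%: SE0 = √(2 × 0.38 × 0.62/152) = 0.0557; SE1 = √((0.2100 + 0.2484)/152) = 0.0549; power 82.3%. The difference detectable at 80% power is 15.5 points, which rounds to the stated 16.
- Aim 3, 27% vs 42.3%: SE0 = 0.0546; SE1 = 0.0539; power 80.3%. The detectable difference is 15.2 points, against the stated 15.3.

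Both figures reproduce.

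**Step 2: direction of the effect.** With arms balanced within sites, and site rates having mean p and SD s, the true null variance of the arm difference is proportional to p(1−p) − s². The pooled chi-square uses p(1−p). Its actual type I error is therefore about 2[1 − Φ(1.96/r)], with r = √(1 − s²/[p(1−p)]). At p = 0.30, p(1−p) = 0.21:

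| s | s²/0.21 | r | approximate type I error |
|---|---|---|---|
| 0.05 | 0.012 | 0.994 | 4.9% |
| 0.10 | 0.048 | 0.976 | 4.5% |
| 0.15 | 0.107 | 0.945 | 3.8% |
| 0.20 | 0.190 | 0.900 | 2.9% |
| 0.25 | 0.298 | 0.838 | 1.9% |

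Since r cannot exceed 1, the error cannot rise above nominal by this mechanism.

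**Step 3: simulation.** Settings: 13 unequal sites, about 152 per arm, and site uptake normal with mean 0.30, truncated to 0.02–0.80. Each cell gives the unstratified chi-square, then CMH stratified by PHCS.

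| SD | Type I error | Power, 16 points | Power, 20 points |
|---|---|---|---|
| 0.05 | 5.1% / 5.2% | 82.7% / 82.7% | – |
| 0.10 | 4.6% / 5.0% | 83.3% / 84.0% | – |
| 0.15 | 3.9% / about 5% | 85% / 87% | 95.8% / 96.5% |
| 0.20 | 3.3% / about 5% | 84% / 87% | 96.1% / 97.2% |
| 0.25 | 2.9% / about 5% | 84% / 88% | 96.5% / 97.9% |

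The simulated type I errors follow Step 2. They sit above the approximation at the largest SDs because truncation narrows the realised spread.

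**Step 4: another spread model.** Here site log-odds are normal, the 13 sites are of equal size and 100,000 trials were run per setting.

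- Aim 2, site log-odds SD 0, 0.5 and 1.0: type I error 5.1%/5.0%, 4.6%/5.0%, 3.4%/4.9%; power 82.6%/82.4%, 83.1%/84.1%, 84.6%/88.4%.
- Aim 3, same SDs: type I error 4.9%/4.9%, 4.5%/4.9%, 3.6%/5.1%; power 80.8%/80.6%, 81.1%/82.2%, 82.6%/86.6%.
- At the extreme SD of 1.5 (site rates about 2% to 82%), Aim 2 power is 86.4%/92.5% and type I error 2.3%/4.9%.

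The unstratified test kept at least 80% power in every setting.

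**The case against.** The strongest reply is that the planned test is valid and does its job. Its error can only fall below 5%, it meets the stated 80% power in every setting examined, and at the expected 20-point difference it already has about 96% power. The spread that makes stratification matter is assumed, and at SD 0.10 or below the gain is trivial. The primary aim, a one-sample exact binomial test, is untouched. All of this stands and limits the point to a modest efficiency gain. It does not remove the point, because stratifying costs essentially nothing when sites are alike and holds the nominal level when they differ.

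Stronger readings are tempting, but the article does not support them:

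- *Sites are the unit of allocation, so clustering invalidates the chi-square.* The phrase about randomizing at the PHCS level could suggest this, but blocks allocate participants and both arms exist within each PHCS.
- *The test overstates significance, or the trial is underpowered.* Steps 1 to 4 show the opposite on both counts.
- *The plan yields only a p-value.* Study outcomes defines secondary outcomes 2 and 3 as differences in proportions. How the interval is reported is something an article may leave to the full plan.
- *Pooling is wrong because Christchurch screens differently before randomization.* With 1:1 allocation within each PHCS, site does not confound the crude comparison. A Mantel-Haenszel estimate also combines all sites, so it would not answer a question about effect heterogeneity.

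**Conclusion.** The point holds as a minor one, confined to secondary Aims 2 and 3. The analysis ignores the stratum used for allocation. If uptake differs between PHCS, the test is conservative, with type I error of about 3.9% to 2.9% at assumed SDs of 0.15 to 0.25. Power given up at a 16-point effect is nil at SD 0.05, 0.7 points (84.0 − 83.3) at 0.10, and about 2 to 4 points at 0.15 to 0.25. At 20 points it is 0.7 to 1.4 points. The stated detectable differences and 80% power are not in question.

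These sizes depend on the assumed spread, for which the article gives no figure, and on within-site balance largely surviving the post-randomization exclusions. The direction does not depend on the size of the spread.

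**What to change.** In Statistical analyses, for Aims 2 and 3:

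- Replace the Pearson chi-square with a Cochran-Mantel-Haenszel test stratified by PHCS.
- Report the Mantel-Haenszel risk difference with its 95% CI.
- Set a size threshold below which a PHCS is merged with others under the same tertiary hospital, fixed in advance and blind to outcome, so that merging is not a data-dependent choice.
- Keep the crude chi-square as a sensitivity analysis.

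The cost is a short change of wording plus the merging rule. PHCS is already known for every participant because allocation uses it, the method is standard in the planned software, and the sample size need not change.

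### Aims 2 and 3 rest on an unadjusted chi-square although plausible predictors of uptake are recorded at screening before randomization: a missed efficiency in valid secondary comparisons, not an error

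*Protocol article*

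**What the plan says.** The Statistical analyses section of the protocol article sets the comparison for Aims 2 (starting treatment) and 3 (SVR12): "Pearson chi-square tests [26] of independence will be undertaken in comparing differences in DAA therapy initiation and SVR12 across the two study groups". The reason offered is "given the individual-level randomized nature of the design". The section mentions no covariate, no term for PHCS and no adjusted model.

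The Data sources section lists what is collected at screening: demographic and social items (among them age, employment, accommodation and incarceration history), injecting history and frequency, "receipt of OST, frequency and quantity of alcohol consumed via the AUDIT-C questionnaire", and wellbeing and mental-health scales. The Randomization section states that "patients are randomized at the end of the screening visit". It adds that some screening procedures come later: in Australia and Auckland, transient elastography (TE) follows randomization and its location depends on the arm. Allocation is blocked within PHCS.

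Secondary objectives 2 and 3, and the matching outcomes, are expressed as differences in proportions between arms.

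**The concern.** Whether a person starts treatment plausibly depends on housing, current injecting, opioid substitution and alcohol use. All of these are on file for each participant at the visit that ends in allocation. Aim 3 counts SVR12 over all participants (its 27% control rate is 30% × 90%), so it is driven mainly by uptake as well.

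A 2×2 test uses none of this information. If the items are prognostic, an adjusted risk difference estimates the same marginal quantity with a smaller standard error and needs no further data collection. Interval width matters beyond the p-value, because Aims 4 and 5 feed these results into epidemic and cost-effectiveness models. The article also describes serious recruitment difficulty, so precision may not be recoverable by enrolling more people.

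**Working it through.** **Inputs from the article.** Randomized: "we estimated that 190 study participants were required in each arm". Loss after randomization: "we estimated 20% of participants would have screening TE results greater than 9.5 kPa, and would be excluded after being randomized", so 190 × 0.8 = 152 per arm. This agrees with "A sample of 76 (50% of 152) participants commencing DAA treatment at the PHCS". Allocation: "equal allocation across study groups". Aim 2: control 30%, detectable difference 16 points. Aim 3: control 27%, detectable difference 15.3 points. Both use 80% power and 5% significance (two-sided assumed). Planned rates: uptake 50% vs 30%; with 90% cure, SVR12 45% vs 27%.

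**Step 1: reproduce the plan's figures.** Pooled-variance power is Φ{[d√n − 1.96√(2p̄(1−p̄))] / √(p0(1−p0) + p1(1−p1))}.

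- Aim 3, 27% vs 42.3%, n = 152: (1.886 − 1.319)/0.664 = 0.854, power 80.4%. Solving for 80% power gives 15.2 points, so 15.3 reproduces.
- Aim 2, 30% vs 46%, n = 152: (1.973 − 1.345)/0.677 = 0.926, power 82.3%. Solving for 80% gives 15.5 points (16.2 with continuity correction), consistent with a rounded 16.
- At the planned rates: 94.9% for Aim 2 and 90.9% for Aim 3.

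**Step 2: gain from adjustment.** The article reports no association between any screening item and either outcome, so strength is an assumption. Let x be a standard-normal prognostic score and m_a(x) = expit(α_a + s·x), with α_a set so that the arm averages are 30% and 46%.

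- Unadjusted variance: [p0(1−p0) + p1(1−p1)]/n = (0.21 + 0.2484)/152, SE 0.0549. Power is Φ(0.16/0.0549 − 1.96) ≈ 83.0%. This unpooled version is slightly above the 82.3% of Step 1.
- Standardized (adjusted) variance: {E[m0(1−m0)] + E[m1(1−m1)]}/n + Var(m1 − m0)/(2n).

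| Score SD s (assumed) | Variance reduction | Power at 30% vs 46% | Equivalent n per arm = 152/(1 − reduction) |
|---|---|---|---|
| 0.2 | 0.9% | 83.3% | 153 |
| 0.3 | 2.0% | 83.7% | 155 |
| 0.5 | 5.2% | 84.9% | 160 |
| 0.75 | 10.5% | 86.9% | 170 |
| 1.0 | 16.4% | 89.0% | 182 |

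For scale, at 40% overall uptake one binary item with prevalence 20–50% explains about 2–3% of outcome variance at an odds ratio of 2, 5–7% at 3 and 10–14% at 5.

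**Step 3: check by simulation.** With 3,000 simulated trials per setting, the ratio of adjusted to unadjusted variance was 0.97, 0.96, 0.88 and 0.84 at SD 0.3, 0.5, 0.8 and 1.0, in line with the formula. A separate run gave type I error of 4.8% adjusted and 5.4% unadjusted (SD 0.75, 30% in both arms). With covariates that predict nothing, power was 82.1% and 82.4% for the two analyses, no material difference.

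**Step 4: planned rates and shortfall.** At 50% vs 30% the same formula moves power from 95.3% to 95.5%, 96.2%, 97.0% and 97.8% at SD 0.2, 0.5, 0.75 and 1.0. At 45% vs 27% it moves from 91.4% to 91.7%, 92.7%, 94.0% and 95.3%. If only 100 per arm were evaluable (an assumption), Aim 3 power by the Step 1 formula at 27% vs 45% would be 75.9%. It would be 80.2% if covariates explained 10% of the variance (equivalent n 100/0.9 = 111). At 76 per arm the figures are 64.0% and 68.6%.

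**The case against.** The strongest reply is that nothing here is wrong. Under individual randomization the Pearson chi-square is a valid test, it agrees with the power calculation, and its error rate already allows for chance imbalance. The primary aim, a one-sample exact test, is untouched. Adjusted models are often set out in an analysis plan, which was not available for this review. All of this stands, and it limits the point to efficiency.

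Three stronger readings are tempting but unsupported.

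- A reader might infer that strong predictors are being discarded. The article gives no association with uptake or SVR12, so *plausible* is as far as one can go. One item with an odds ratio of 2 is worth about one power point.
- A reader might infer that the plan yields only a p-value. The objectives and outcomes already fix the difference in proportions as the effect measure; what the analysis text lacks is an interval, which needs no covariates.
- A reader might expect adjustment to remove chance imbalance. It deals only with the items modelled.

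The calculation is also somewhat generous: it uses one perfectly measured score, whereas the real items are mostly self-reported and their coefficients must be estimated. Choosing covariates late in an open-label trial that has recruited since November 2015 carries some cost to credibility.

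Against this, the unadjusted test is a stated choice rather than a silence. Individual randomization explains why it is valid, not why baseline information should go unused.

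**Conclusion.** The point holds as a missed efficiency in two secondary aims. The planned test is sound and adequately powered at the planned rates if 152 per arm are evaluable. Adjusting for pre-randomization items would cut the variance of the Aim 2 risk difference by about 1–2% if they are weakly prognostic, 5–10% if moderately so, and 16% at a score SD of 1.0. At 30% vs 46% that is under 1, about 2–4, and 6 power points. At the planned rates it is 0.2 to 2.5 points for Aim 2 and 0.2 to 3.8 for Aim 3. The gain matters more if the initial target of 380 is missed. All these sizes rest on an assumed covariate strength, and the article does not show which row of the table applies.

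**What to change.** Before anyone sees data by arm, prespecify for Aims 2 and 3 a logistic model with:

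- arm;
- PHCS, because allocation is blocked on it;
- a short list of screening items, for example age, current opioid substitution, recent injecting, AUDIT-C and accommodation.

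Use only items recorded before allocation was revealed, and leave out TE where it follows randomization. With 13 services, also fix in advance how very small ones are pooled. Report a standardized risk difference with a 95% CI, and keep the unadjusted difference and the chi-square as the supporting analysis.

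The cost is a few sentences and modest programming, with no new data. The one real downside is fixing the list late in an open-label trial. A dated, documented decision by people without access to by-arm outcomes limits it.
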